## Abstract

**Background:**

Different approaches have been used by dentists to base their decision. Among them, there are the aesthetical issues that may lead to more interventionist approaches. Indeed, using a more interventionist strategy (the World Dental Federation - FDI), more replacements tend to be indicated than using a minimally invasive one (based on the Caries Around Restorations and Sealants—CARS). Since the resources related to the long-term health effects of these strategies have not been explored, the economic impact of using the less-invasive strategy is still uncertain. Thus, this health economic analysis plan aims to describe methodologic approaches for conducting a trial-based economic evaluation that aims to assess whether a minimally invasive strategy is more efficient in allocating resources than the conventional strategy for managing restorations in primary teeth and extrapolating these findings to a longer time horizon.

**Methods:**

A trial-based economic evaluation will be conducted, including three cost-effectiveness analyses (CEA) and one cost-utility analysis (CUA). These analyses will be based on the main trial (CARDEC-03/NCT03520309), in which children aged 3 to 10 were included and randomized to one of the diagnostic strategies (based on FDI or CARS). An examiner will assess children’s restorations using the randomized strategy, and treatment will be recommended according to the same criteria. The time horizon for this study is 2 years, and we will adopt the societal perspective. The average costs per child for 24 months will be calculated. Three different cost-effectiveness analyses (CEA) will be performed. For CEAs, the effects will be the number of operative interventions (primary CEA analysis), the time to these new interventions, the percentage of patients who did not need new interventions in the follow-up, and changes in children’s oral health-related quality of life (secondary analyses). For CUA, the effect will be tooth-related quality-adjusted life years (QALYs). Intention-to-treat analyses will be conducted. Finally, we will assess the difference when using the minimally invasive strategy for each health effect (∆effect) compared to the conventional strategy (based on FDI) as the reference strategy. The same will be calculated for related costs (∆cost). The discount rate of 5% will be applied for costs and effects. We will perform deterministic and probabilistic sensitivity analyses to handle uncertainties. The net benefit will be calculated, and acceptability curves plotted using different willingness-to-pay thresholds. Using Markov models, a longer-term economic evaluation will be carried out with trial results extrapolated over a primary tooth lifetime horizon.

**Discussion:**

The main trial is ongoing, and data collection is still not finished. Therefore, economic evaluation has not commenced. We hypothesize that conventional strategy will be associated with more need for replacements of restorations in primary molars. These replacements may lead to more reinterventions, leading to higher costs after 2 years. The health effects will be a crucial aspect to take into account when deciding whether the minimally invasive strategy will be more efficient in allocating resources than the conventional strategy when considering the management of restorations in primary teeth. Finally, patients/parents preferences and consequent utility values may also influence this final conclusion about the economic aspects of implementing the minimally invasive approach for managing restorations in clinical practice. Therefore, these trial-based economic evaluations may bring actual evidence of the economic impact of such interventions.

**Trial registration:**

NCT03520309. Registered May 9, 2018. Economic evaluations (the focus of this plan) are not initiated at the moment.

**Supplementary Information:**

The online version contains supplementary material available at 10.1186/s13063-021-05722-7.

## Background

Reinterventions in restored teeth are common procedures in dentistry. Caries lesions around restorations, frequently denominated as “secondary caries,” have been identified as the main reason for repairing or replacing the restorations in primary teeth [1]. The detection of these lesions and other aspects related to defective restorations in primary teeth is challenging as it involves a clinical inspection of the dental surface and the restorative material as well as their interface. The visual-tactile method is commonly used for this purpose. Some clinical strategies based on this method have been proposed to standardize the clinical assessment of restorations and support treatment decisions [2].

In general, dentists base their decision on different parameters, including aesthetical ones. This option tends to result in a more interventionist approach. In 2007, the World Dental Federation (FDI) proposed a strategy to evaluate restorations comprising aesthetic, functional, and biological parameters, including the presence of caries and related aspects [3]. The FDI criteria were proposed for research and clinical practice and used to decide reintervention in restored teeth [4]. Due to the several aesthetic parameters evaluated, the diagnostic strategy based on FDI embraces a cosmetic dentistry perspective, relating to a more interventionist approach for the clinical practice.

On the other hand, the caries associated with restorations and sealants (CARS) strategy is a more recently minimally invasive strategy proposed as part of the International Caries Classification and Management System (ICCMS) [5] and exclusively focused on detecting caries lesions around the restorations [6]. The CARS strategy is based on the International Caries Detection and Assessment System (ICDAS) scores. It is more consistent with a Cariology background, leaning on a less interventionist approach, based solely on the occurrence of caries lesions and their characteristics.

To date, there is no consensus on the best strategy to adopt in clinical practice, and most studies do not explore the clinical relevance of the accuracy tests nor patient-centered outcomes [2]. An ongoing clinical trial (CARies DEtection in Children - CARDEC-03) aims to assess the impact of using the FDI and CARS criteria in the assessment of restorations in primary teeth [7]. At first glance, when using a more interventionist strategy (using the FDI criteria), the indication of replacements of restorations in the baseline was more frequent than using the strategy based on CARS [8]. Nevertheless, the resources related to the long-term health effects have not been explored yet.

When defective restorations in primary teeth need to be assessed to guide their management, it is not known if this minimally invasive strategy is efficient for allocating resources compared to the conventional strategy, based on FDI criteria. Even if the diagnostic method benefits patients, the subsequent financial impact should be assessed, featuring phase 5 studies for diagnostic methods [9]. As dental expenditure was $298 billion in 2010, representing 4.6% of global healthcare costs [10], economic evaluations to direct resources to the best diagnostic strategies are critical for clinical practice to be financially viable. On the other hand, economic evaluations assessing diagnostic strategies are scarce and, in several cases, are not standardized and present low quality [11].

We are presenting a health economic analysis plan to guide a trial-based economic evaluation. The publication of the health economic analysis plan has been becoming the best practice for trial-based economic assessments. Publishing an economic analysis plan is currently relevant since it increases the reproducibility, dissemination to other research groups, and transparency of the analyses. Indeed, this process intends to guarantee that the process avoids selection bias related to data sources and valuation methods, selective reporting in results, and the use of unplanned analyses to satisfy a specific hypothesis [12, 13]. The present health economic analysis plan aims (1) to describe methodologic strategies for conducting a transparent trial-based economic evaluation that aims to assess whether a minimally invasive strategy is more efficient in allocating resources than the conventional strategy for managing restorations in primary teeth and (2) to construct a decision analytic modelling framework to extrapolate these findings considering a primary molar lifetime horizon.

## Methods

This manuscript is a health economic analysis plan following the International Society for Pharmacoeconomics and Outcomes Research (ISPOR) Good Research Practices Task Force Report recommendations [14] and the Consolidated Health Economic Evaluation Reporting Standards (CHEERS) [15] checklist.

### Study design

A trial-based economic evaluation will be conducted (piggyback approach), including three cost-effectiveness analyses (CEA)—different health effects—and a cost-utility analysis (CUA). The clinical trial investigating the diagnostic strategy for restorations assessment is the third diagnostic study conducted by the CARDEC collaborative group at the School of Dentistry of the University of São Paulo (São Paulo, Brazil). The CARDEC-03 trial is a two-arm, parallel-group, patient-randomized controlled trial aiming to assess which diagnostic strategies (based on FDI criteria or CARS) leads to fewer new interventions in restored primary teeth during 2 years of follow-up. Further details regarding the trial have been published in the study protocol [7].

The strategy based on the FDI criteria will be acknowledged as the reference strategy for assessing the restorations. However, recognize there is no robust evidence supporting this assumption. Despite this, a reference strategy for economic evaluation must be assumed. Considering that the CARS strategy is associated with a less interventionist approach, we will consider it as the new strategy. Moreover, FDI criteria were first proposed and appointed by experts as the standard criteria for restorations’ assessment [16, 17].

### Target population and eligibility criteria

Children’s participation was voluntary. Our sample includes 3-to-10-year-old children seeking dental care at the Pediatric Dentistry clinic from our school, with at least one dental restoration in a primary tooth. The exclusion criteria were children whose parents did not consent to their participation, children who did not assent participating in this study, and children with limited ability to co-operate even when behavior management was used [18].

### Comparators—interventions and follow-up

Aiming to compare a more interventionist strategy to a supposedly less interventionist approach when assessing dental restorations and guiding clinical decision-making, children were allocated to one of the two diagnostic strategies for the assessment of restorations. To simplify, we will refer to them, from that point, as FDI and CARS strategies. A trained and calibrated examiner ([name]) performed the assessments, and treatment decisions were based on the criteria. The FDI criteria [16] can be adapted depending on the purpose of the study. Therefore, since dental caries is the most common reported reason for reinterventions in primary teeth, we chose to evaluate related parameters as marginal staining and adaptation, besides the recurrence of caries. The CARS strategy will be used as originally proposed [5] (Table 1). Details regarding clinical criteria, sample size, randomization, allocation, blinding, and treatment of the restorations have been previously described in a clinical trial protocol [7].

**Table 1 Tab1:**
[figure not shown]
Clinical strategies for FDI and CARS criteria—adapted from Moro et al. [7]

^1^Based on Hickel et al. [16]

^2^Based on Pitts et al. [14]

Children will be followed for 24 months after the baseline interventions. Clinical assessments are being scheduled at 6-month intervals. In the baseline and at each follow-up visit, children are being instructed about diet and oral hygiene. The same examiner responsible for baseline evaluation will reassess the restorations at each appointment and propose a new treatment plan for each child based on the randomized strategy.

### Time horizon, study perspective, and discount rate

The time horizon for the main evaluations was set as 24 months (time of study enrollment). Secondary longer-term economic evaluation with trial results will be performed to extrapolate the results over a primary tooth lifetime horizon. We will adopt the societal perspective, accounting for direct and indirect costs. A discount rate of 5% will be applied for costs and effects as the trial is being conducted in Brazil, a lower-middle-income country [19]. Further sensitivity analyses will test the influence of this assumption by considering different discount rates (0–10%).

### Costs and resources

The costs of each strategy will be estimated using a micro-costing approach. The direct and indirect costs per tooth and child will be calculated over 24 months (Supplemental Material 1). Direct costs will comprise the expenses related to the dental office accommodation, dental instruments and equipment and their respective maintenance, materials used to implement the strategies, and staff expenses (based on working hours and time spent on patient’s care). Firstly, direct costs will be estimated per tooth included in the trial. Then, we will sum up all the child’s eligible teeth for calculating direct costs with each child.

We will calculate the accommodation costs using rental costs and municipal taxes per square meter of the area used by each dental unit. Subsequently, the accommodation costs per hour will be calculated. The same calculation will be used for dental instruments and equipment, estimating a life span of 3 years for instruments [20] and 5 years for equipment [21], with a monthly usage of 160 h. The staff salary (dentists and dental auxiliaries) will be calculated based on the Brazilian Federal Law’s monthly wage, allowing 40 h per week (8 h/day) for each dentist and dental nurse. For dental material, we will calculate the mean value of each item in three different dental stores and quantities used during clinical appointments.

Indirect costs will include out-of-pocket expenditures, such as transportation (public or private), any opportunity costs of accompanying a person’s absence from the workplace, and the patient’s time accessing care. These costs will be estimated per child, considering the time spent during appointments and waiting or travelling to/from the dental clinic. For indirect costs per tooth, time spent performing procedures related to each specific tooth will be first considered. For the child’s general appointments (e.g., instructions, fluoride applications) and the child’s and accompanying person’s waiting/travelling, the time spent will be fully considered for each tooth, as if only one tooth had been included per child. Possible dental interventions received externally to the research, but related to the assessed teeth, will also be considered indirect costs.

Transportation costs will be calculated using the municipality’s fares for public transportation. For private transport, we will consider the distance from the family’s house to the University and an average price for fuel obtained from the Brazilian National Agency, assuming an 8 km per liter efficiency. The patient’s and accompanying person’s time will be valued, respectively, based on the Brazilian minimum wage and mean Brazilian salary. Suppose the accompanying person reports any earning loss due to being present at the child’s appointments, an additional cost of a working day will be added for each appointment the child attends. The accompanying person’s working absence time will also be calculated based on the mean Brazilian salary. In this case, the working days and hours will be considered to estimate this person’s value per working hour.

To estimate the costs, we have registered in a specific form the number of appointments, the time spent at each one, and materials used during patient care (Supplemental Material 2). This form has also been used to collect information about transportation and absence from work. Details about the cost estimation of each of the resources mentioned above can be found in Supplemental Material 1.

Costs will be calculated in Brazilian Real (BRL) considering the base year for the analysis and converted to international dollars using purchasing power parities (PPP) measured for the same period (or the most recent indicator available at the time of the analyses).

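### As worded, an accompanying adult who reports an earning loss is charged twice for the same time: by the hour and again as a full working day

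*Protocol article*

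**What the plan says.** The rules for the adult's time are all in the Costs and resources section of the protocol article.

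- **Hours covered.** Indirect costs, including the adult's absence from work and time, are built up per child, "considering the time spent during appointments and waiting or travelling to/from the dental clinic".
- **Unit value of those hours.** The patient's and the "accompanying person’s time will be valued, respectively, based on the Brazilian minimum wage and mean Brazilian salary". So the adult's hours carry the mean salary, and adults who also lose earnings are not excepted.
- **Trigger for a second charge.** "Suppose the accompanying person reports any earning loss due to being present at the child’s appointments". No minimum amount or duration is set.
- **Size of the second charge.** In that case "an additional cost of a working day will be added for each appointment the child attends".
- **Unit value of the second charge.** The adult's "working absence time will also be calculated based on the mean Brazilian salary", converted to a value per working hour.
- **Data.** "This form has also been used to collect information about transportation and absence from work".

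The section refers to Supplemental Material 1 for costing details and to Supplemental Material 2 for the form. Neither is shown.

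**The concern.** An adult who misses work to bring a child to the clinic loses one block of time. The hours in the chair-side visit, the waiting room and on the way there and back normally lie inside that block. The rule prices those hours and then adds a whole working day at the same salary, so the overlapping part is paid for twice. It is hard to defend the two charges as lost leisure plus lost work, because the day is triggered by earnings lost through being at the appointment.

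The same sentence raises a second question: on which visits does the extra day fall? It can be read as every visit the child attends once any loss has been reported, or as only the visits at which a loss occurred.

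The item is not peripheral. The article adopts a societal perspective, so the adult's time enters total cost, the cost difference (CARS minus FDI) and the incremental net benefit. Trial costs also supply the Markov model for the primary tooth lifetime, so an error in the costing rule would carry into the extrapolation.

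**Working it through.** The article gives no total for this item, so there is no stated figure to reproduce. The check counts mean-salary hours charged to one adult under the rule as worded and compares them with charging the time once.

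**Inputs**

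- D = 8 hours in a working day. Costs and resources gives this for dentists and dental nurses only, so applying it to the adult is an assumption.
- h = hours per visit for appointment, waiting and travel. The article gives no figure, so h = 1 to 4 is an assumed range.
- V = 5 scheduled assessments: baseline plus 6, 12, 18 and 24 months, from the 6-month schedule and the 24-month follow-up. Treatment visits would come on top.
- Both charges use the mean Brazilian salary, so hours can be added directly.

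**Step 1. One visit with a reported loss**

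As worded: h + D. Charged once, as a full lost day: D. Ratio: (h + 8)/8 = 1 + h/8.

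| h (assumed) | As worded | Day only | Excess over a full day |
|---|---|---|---|
| 1 | 9 h | 8 h | 12.5% |
| 2 | 10 h | 8 h | 25% |
| 3 | 11 h | 8 h | 37.5% |
| 4 | 12 h | 8 h | 50% |

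This takes all h hours to lie inside the lost day. If part of the travel falls outside working hours, only the overlapping part is duplicated. If the true absence was shorter than a day, the overcharge is larger: where only the attendance hours were lost and h = 3, the rule charges 11 h for 3 h, or 3.7 times.

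The sentence on absence time is most plausibly how the lost day is valued, and it is treated that way here. If it were a separate item, it would be a third charge.

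**Step 2. Which visits carry the day**

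Five visits, with a loss at one of them:

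| Reading | h = 2 | h = 3 |
|---|---|---|
| Day added at every visit (literal) | 5 × (2 + 8) = 50 h | 5 × (3 + 8) = 55 h |
| Day added only at the loss visit | (2 + 8) + 4 × 2 = 18 h | (3 + 8) + 4 × 3 = 23 h |
| Time charged once | 8 + 4 × 2 = 16 h | 8 + 4 × 3 = 20 h |

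Against the last row, the literal reading is 50/16 = 3.1 times and 55/20 = 2.75 times. The narrower reading is 18/16 = 1.125 and 23/20 = 1.15 times. The narrower reading removes the carry-over but leaves the overlap of Step 1.

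**Step 3. The cost difference**

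Let p be the share of visits at which a loss is reported, n the mean number of appointments per child in an arm, and w the hourly value. Take the narrower reading, with p and h equal in both arms. The duplicated amount per child is then p × h × w × n, and its contribution to the cost difference (CARS minus FDI) is p × h × w × (n for CARS − n for FDI). The article gives no values for p, h or n by arm, so this cannot be evaluated. It is zero if the arms have equal numbers of appointments, and it adds to the cost of whichever arm has more.

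**The case against.** The strongest objection is that the operative rule may lie elsewhere. The article sends the reader to Supplemental Material 1 for costing details, and that document might net the hours out of the day. This limits certainty but does not remove the point. The article does not leave the matter open; it states a rule in which the day is added. If the supplement differs, the two need to be reconciled.

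Four stronger readings are tempting, and the documents do not support them.

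- **That one reported loss certainly loads every visit.** The literal wording says so, but the trigger refers to loss from being present at appointments, and the form records data by appointment. A rule of one day per appointment with a loss is a fair reading. The wording is ambiguous.
- **That the main cost contrast is biased towards CARS.** Assessments are scheduled 6-monthly for all children, so the overcharge on those visits should largely cancel between randomised arms. Only a difference in other appointments transmits it. FDI would have more under the plan's own hypothesis, but the Discussion allows that restorations left alone may produce a different picture. The direction is conditional and the size unknown.
- **That costs are overstated by 25% to 50%.** That range concerns one cost item, at affected visits only, under assumed hours. It is not a share of indirect, total or incremental cost.
- **That the form already holds what a correction needs.** The article says only that absence from work was recorded. Whether its duration was recorded, visit by visit, is not shown.

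The planned one-way sensitivity analysis on costs could show whether the item matters. It would not correct the base-case rule.

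**Conclusion.** The concern holds for the rule as worded. An adult who reports any earning loss is charged attendance, waiting and travel hours plus a full working day, both at the mean salary, and the overlap is counted twice. With an assumed 8-hour day and 2 to 4 hours per visit lying within it, the excess is 25% to 50% for this item at affected visits. Whether the day also spreads to visits without a loss is unclear from the text. If it does, the overcharge for such an adult is much larger, as the five-visit example shows. The effect on the cost difference cannot be computed. Adults who report no loss are unaffected.

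Confidence is medium, because Supplemental Material 1 and the data form are not shown. The point should be corrected before the costs are analysed.

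**What to change.** Charge the accompanying adult's time once per visit:

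- Where an earning loss is reported for that visit, charge the lost work time in place of the hourly charge. Use the recorded absence if the form gives its duration, otherwise one working day.
- Where no loss is reported for that visit, charge the appointment, waiting and travel hours only.
- State that the lost-time charge applies only to visits with a reported loss, as far as the form allows this to be identified.
- Show the additive full-day rule as a sensitivity analysis, so that its influence on the cost difference can be seen.
- Reconcile the text of Costs and resources with Supplemental Material 1.

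The rule still works if the form holds no more than a yes or no per visit, because the one-day default then applies. The cost is a small change to the costing code and somewhat lower indirect costs. The article states that the economic evaluation has not begun, so the change can be made before any result is known.
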